**Termination stage (ending MOUD)^i^**			
	Strong desire to terminate treatment	Referring to a physician for support and to prevent overdose Reiteration of the importance of long-term treatment	Approachability Acceptability Appropriateness Ability to perceive Ability to engage
**Recurrence (or relapse) stage^j^**			
	Stigma or shame around recurrence. The belief that recurrence is a “failure” [35]	Research on recurrence as a natural occurrence of OUD and opportunity for readjustment	Approachability Ability to perceive Ability to engage
	Belief that recurrence is long-term	How to return to treatment	Approachability Acceptability Appropriateness
	Lack of strategies to prevent recurrence [32]	Create a recurrence prevention plan	Ability to seek Ability to engage
	High risk of overdose during recurrence	Revisit harm reduction resources	Approachability Ability to perceive

^a^Precontemplation stage MI check-in questions: readiness rulers [36]—How important is it for you to change your opioid use? What made you choose that number and not a lower one? What would help you pick a higher number? How confident are you in making this change? What would help you be more confident?

^b^OUD: opioid use disorder.

^c^MOUD: medications for opioid use disorder.

^d^HCV: hepatitis C virus.

^e^Contemplation stage MI check-in questions: How does your current opioid use affect your life, relationships, career, and future goals? How would treatment help you resolve some of those and help you achieve your goals?

^f^Preparation stage MI check-in questions: What are the ways to address some of the challenges you are worried you may face? What are the steps you may need to take to receive treatment?

^g^Action stage MI check-in questions: What has been working well for you? Are there any places that you need to strengthen to help your progress?

^h^Maintenance stage MI check-in questions: What challenges have you been encountering? What are practical ways to address them? Can you name 3 things that have improved since starting treatment?

^i^Termination stage MI check-in questions: readiness rulers [36]—How confident are you in making this change?

^j^Recurrence (or relapse) stage MI check-in questions: How has this relapse gotten me closer or farther away from my treatment goals? What do you think you need to help you in your next steps?

**Figure 2 figure2:**
[figure not shown]
A snapshot of the preparation stage home page of the MOUD Hub. Each stage has a home page with a description of the stage and a tailored affirmation at the top, followed by tabs for different themes relevant to the stage. For the preparation stage, the themes are where to obtain medications for opioid use disorder (MOUD), recovery support groups, transportation, pharmacy, cost of MOUD, storing medication, treatment during pregnancy, preparing for stigma, who can I call in a crisis, friends and family, and check in. SAMHSA: Substance Abuse and Mental Health Services Administration.

**Figure 3 figure3:**
[figure not shown]
An example of a check in box for the precontemplation stage. Each stage has a tailored check in with questions guided by the principles of motivational interviewing. Users will be able to answer the questions and download them to their personal devices.

Apps deemed useful, such as the Calm App, were added as resources. Although we recognize that some apps may not be tested through randomized controlled trials, we chose those that have been based on helpful practices, such as mindfulness and harm reduction [37]. The *MOUD Hub* informs users that these apps may not be evidence based but that they might find some of them useful when trying to use coping skills for their treatment.

The website explicitly includes disclaimers regarding the fact that it does not offer medical advice; the language used, which in some instances includes terms from other resources that may be considered stigmatizing and for which we have used quotation marks; and noting that the resources are compiled rather than created by us (Multimedia Appendix 2).

### Accessibility

The website has tabs to organize how users access the resources. For example, there is a “Languages” tab showing users how to set up and enable translations in their web browser if English is not their preferred language, as well as an “Audio” option that informs users on how to have the website read to them to reduce access barriers among those with vision or literacy concerns. The website was developed to be accessed from a computer and a mobile phone to increase accessibility.

### Dissemination

The dissemination of the *MOUD Hub* will follow web-based marketing strategies, which harness interest in a topic, as expressed by internet searches or membership to specific social media networks, to promote the resource and increase its uptake. We will use internet searches on Google and leverage Reddit subreddits or discussions focused on opioid use recovery, treatment, and overdose prevention.

For Google, we will advertise this website in response to specific searches using sets of words described by Patton et al [18]. For example, when someone googles “opioid+treatment,” they will see our advertisement. For Reddit, the website will be posted monthly in the subreddits of r/Methadone, r/suboxone, r/OpiatesRecovery, and r/Naloxone. We will advertise the *MOUD Hub* monthly and tailor the post to incorporate the month’s most discussed topic. The monthly frequency of the posts is driven by the subreddits’ constraints on the maximum number of research-related posts.

### Recruitment, Sample, and Participants

To evaluate the safety and preliminary acceptability before advertising the website, we will first carry out pilot focus groups with 10 graduate students with lived experience of OUD, personally or through family and friends, and who are participating in recovery groups or unions for people who use drugs. In these focus groups, we will pay particular attention to safety and make changes to the MOUD Hub accordingly. Participants will be recruited by contacting UC San Diego and San Diego State University student recovery groups.

After the pilot focus groups have been conducted and relevant changes have been made, 4 additional focus groups will be conducted with people living with OUD who have never received MOUD; people living with OUD who have experience with MOUD; family and friends of someone using opioids (including people living with OUD); and individuals who work with people living with OUD, including MOUD providers, counselors, and harm reduction workers. Each focus group will aim to have 4 to 8 participants. Participants will be recruited from MOUD treatment centers, support groups for family or friends of people living with OUD, and harm reduction organizations in San Diego through email to ask for permission to share study fliers. The purpose of these focus groups will be to gain more in-depth knowledge on the safety and acceptability of the hub, user experience, and thoughts on its usefulness in improving MOUD access and retention.

For all focus groups, participants will have the option of engaging in a focus group either through Zoom (Zoom Video Communications) or in person. Inclusion criteria for participants include being aged ≥18 years and having at least one of the aforementioned experiences. Exclusion criteria include experiencing severe mental health issues and being unable to provide informed consent.

There are no eligibility criteria for the study when assessing the website’s reach due to it being available for public access. We will be openly advertising it to people who make relevant Google searches or who are members of opioid-related subreddits. Similarly, there is no randomization, as all users can access the same website’s content. We will be able to identify whether participants came from Reddit or Google and treat them as 2 different samples. This will enable us to investigate differences in user volume and characteristics when accessing the website through Reddit or Google and to evaluate the most appropriate platform for dissemination for future-related interventions.

There is potential for bias, including misclassification, self-selection, and response bias. It will not be possible to know whether users are experiencing OUD or searching for information for a loved one, limiting our understanding of the representativity of the sample by OUD experience and leading to potential misclassification bias. However, we will be able to know whether users clicked on resources specific to friends or family and whether they responded to the “check-in” questions directed at people living with OUD. In addition, the pop-up survey asks whether users are accessing the website for themselves or a friend or family member. This will provide us with an additional measure for the proportion of users who are seeking help for themselves versus for a friend or family member.

Effectively, all people accessing the website will self-select based on need or curiosity, and we will miss information from people living with OUD who are not seeking help for OUD or are not compelled to access the *MOUD Hub* when exposed to it. The demographics data will allow us to assess to what extent our sample is representative of the general population and the population experiencing OUD and fatal overdoses in the United States in terms of geography, age, and gender. We will also be able to assess whether users are accessing the website from Google, Reddit, or other sources, potentially representing different communities. While response bias is possible in the context of our pop-up survey, participation will be voluntary and anonymous, and therefore, this will be minimized. However, there will undoubtedly be self-selection bias among the group answering the survey, likely representing those most engaged in improving access to reliable MOUD information*.*

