### Outcomes and Measures

To evaluate the safety and acceptability of the *MOUD Hub*, we will conduct pilot focus groups with 10 graduate students belonging to recovery groups or unions for people who use drugs. We will lead 2 focus groups to explore safety-related issues, along with gaining feedback on the acceptability, content, and any additional information that should be provided on the website. Safety concerns will focus on, but will not be limited to, information that may potentially be triggering or misleading and stigmatizing language.

A total of 4 additional focus groups will be conducted with other groups to gain more in-depth knowledge on the acceptability of the hub, user experience, and thoughts on its usefulness, following improvements from the pilot focus group. The topic guide in Multimedia Appendix 3 will be used.

To evaluate the reach and use patterns of the website, we will use Google Analytics to collect data on the number of users, their characteristics, and their interactions with the website [38,39]. The website will be launched in January 2025, and we will collect data for evaluation for a year and look at the data in 3-month increments. With this iterative approach, we can adjust the website in real time.

Our protocol’s outcomes and measures are shown in Table 2. We will first assess the dissemination reach of the website. The reach of an intervention is defined as “the absolute number, proportion, and representativeness of individuals who are willing to participate in a given initiative, intervention, or program, and reasons why or why not” [40].

**Table 2 table2:** Outline of the quantitative and qualitative measures that will inform the outcomes. Each measure is labeled with the information’s source.

Reach		Acceptability

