**Figure 4 figure4:**
[figure not shown]
A pop-up survey that will be presented to users before they leave the website to collect demographic information and initial acceptability of the website. MOUD: medications for opioid use disorder.

To further assess acceptability, we will measure the proportion of users who return to the website along with using the Acceptability of Intervention Measure [41]. The pop-up survey will ask closed- and open-ended questions to assess acceptability and identify additional relevant resources. The closed-ended questions will use the 4 questions from the Acceptability of Intervention Measure [41]. The open-ended questions will ask about ways in which they found resources helpful, whether there are other topics or questions that they expected to obtain information on but did not find anything relevant, and whether there are any other resources they would like to share with the broader community. Google Analytics tracks the number (and proportion) of people who are returning users, which will be used as another measurement of acceptability.

Finally, we will compare users who come from Reddit versus those who come from Google by looking at the volume of users from each source and their characteristics. The aforementioned outcomes will be assessed to compare the effectiveness of social media versus search engines in disseminating resources such as the *MOUD Hub.*

For the website’s reach, we hypothesize that (1) users will most frequently click on links related to the precontemplation or contemplation phases of MOUD use, as opposed to links related to the preparation, action, and maintenance phases; (2) a substantial proportion of users (>25%) will be family members or friends of people who use opioids; (3) the volume of users referred through Google searches will be larger than that of users referred through Reddit; and (4) users referred through Reddit will spend more time on the website and click on a higher number of links than users referred through Google searches.

For acceptability, we hypothesize the following: (1) most users will find the resource useful and ratings will be significantly higher among acquaintances of people who use opioids than among people who use opioids themselves; (2) users with OUD will find the resource less useful; and (3) a large proportion of resources shared by users will lead to non–evidence-based information, including rehabilitation centers based on mandatory abstinence.

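### The comparison of site users with the OUD and fatal-overdose populations is not split by user type, so neither a match nor a gap can be interpreted as it stands

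*Protocol article*

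**What the plan says.** All places are in the Methods of the protocol article.

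- **Who is in the sample.** Recruitment, Sample, and Participants: "There are no eligibility criteria for the study when assessing the website’s reach". Anyone who reaches the public site counts.
- **What is known about them.** Same section: "It will not be possible to know whether users are experiencing OUD or searching for information for a loved one". The article draws the consequence itself, describing this as "limiting our understanding of the representativity of the sample by OUD experience", and it names misclassification as a possible bias.
- **What is nevertheless to be assessed.** In the next paragraph, the demographics data are credited with letting the team "assess to what extent our sample is representative of the general population and the population experiencing OUD and fatal overdoses in the United States". The variables named for this are age, gender and geography.
- **Who is expected to come.** Outcomes and Measures, second reach hypothesis: "a substantial proportion of users (>25%) will be family members or friends of people who use opioids".
- **What could separate the groups.** Recruitment, Sample, and Participants: "the pop-up survey asks whether users are accessing the website for themselves or a friend or family member". The stated use of this item is to estimate the proportion seeking help for themselves. Clicks on friend/family resources and responses to check-in questions are named as further indicators.
- **Why it bears on an outcome.** Outcomes and Measures adopts a definition of reach that covers "the absolute number, proportion, and representativeness of individuals who are willing to participate".

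Statistical and Qualitative Analyses describes age, gender and location for users as a whole. It does not restrict or stratify the benchmark comparison by user type.

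**The concern.** The reference populations for OUD and fatal overdose consist of people who use opioids. The sample is a mixture that deliberately includes relatives and friends, because the site is built for them too. If relatives and friends differ from people with OUD in age or gender, the all-user profile depends on how many of them visit as well as on which people with OUD are reached.

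The result could mislead in either direction. A false gap could prompt changes at a 3-month review that are not needed. A false match could hide a subgroup of people with OUD whom the site does not reach. Ethical Considerations says that effective and equitable dissemination is to be assessed before a randomized trial, so the answer has a use beyond description.

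**Working it through.** The article gives no figure for this comparison, so there is nothing to reproduce. The check uses the identity for a mixture of two groups, leaving aside any other visitors.

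**Inputs**
- f, the family/friend share: above 0.25 by the plan's hypothesis. 0.50 is an assumed higher value.
- p_self, the share with a characteristic among people visiting for themselves: not in the documents.
- p_family, the same share among family and friends: not in the documents.
- Benchmark share in the OUD population: not in the documents.

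**Formulas**
- All-user share = (1 − f) × p_self + f × p_family
- Distortion relative to self users = f × (p_family − p_self)

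**False gap.** Assume a benchmark of 35% women, matched exactly by self users, and 70% to 80% women among family and friends.

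| f | p_family | All-user share | False gap |
|---|---|---|---|
| 0.25 | 0.70 | 0.75 × 0.35 + 0.25 × 0.70 = 0.4375 | 8.75 points |
| 0.25 | 0.80 | 0.75 × 0.35 + 0.25 × 0.80 = 0.4625 | 11.25 points |
| 0.50 | 0.70 | 0.50 × 0.35 + 0.50 × 0.70 = 0.525 | 17.5 points |
| 0.50 | 0.80 | 0.50 × 0.35 + 0.50 × 0.80 = 0.575 | 22.5 points |

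**False match.** Suppose self users are 20% women, and 25% of users are family or friends, of whom 80% are women. Then 0.75 × 0.20 + 0.25 × 0.80 = 0.35. The all-user share equals the benchmark, and a true deficit of 35 − 20 = 15 points disappears.

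**Second set of assumptions, as a check on sensitivity.** Take a benchmark of 60% for some characteristic, matched by self users, and f = 0.25.

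| p_family | All-user share | False gap |
|---|---|---|
| 0.20 | 0.500 | −10.0 points |
| 0.30 | 0.525 | −7.5 points |
| 0.40 | 0.550 | −5.0 points |
| 0.50 | 0.575 | −2.5 points |
| 0.60 | 0.600 | 0 |

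The last row is the case in which the groups are alike and the problem vanishes. For any fixed pair of group shares the distortion grows with f, so f = 0.25 gives the least distortion compatible with the plan's hypothesis.

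**Effect of splitting.** Among those visiting for themselves f = 0, so the mixing term is 0. Selection into the survey remains.

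**The case against.** The strongest reply is that the article sees the problem. It states that OUD status is unknown, warns of misclassification and names three indicators of user type. Table 2 lists the self/other item among the user demographics, so a split comparison would be compatible with the text. The sentence at issue promises only to assess an extent. The study is descriptive, and no test against external populations and no decision rule for representativeness is planned. The general population is also named as a reference, and family and friends are an intended audience, so all-user demographics are a proper reach result.

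Most of this stands, and it limits the point. The comparison with the general population is unaffected. The size is illustrative only, and the false match requires values that happen to cancel. A reader might infer that the all-user figures say nothing about reaching people with OUD, or that the two paragraphs flatly contradict each other. The documents support neither reading. With the family/friend share and survey demographics by user type, the all-user figures could be interpreted, and the paragraphs can be read as a caveat followed by a claim that is too broad.

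The reply does not remove the core. The caveat is not carried into the sentence on the OUD and overdose populations, the survey item is given only the task of estimating a proportion, and the analysis section does not split the comparison. This is more than detail left to a fuller document, because the article itself says that the data will support the assessment.

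**Conclusion.** The point holds as one of interpretation. Following the text compares a mixed group with benchmarks that describe one of its parts, so a match or a gap with the OUD or overdose population cannot be interpreted without user type.

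The distortion is f × (p_family − p_self). Under the assumed gender shares it runs from about 9 to 23 points, or yields a false match that hides 15 points. It falls to zero if family and friends resemble self users. None of the gender shares is in the documents, and the 25% is a hypothesized threshold. No figures were worked for age or geography. This is a worthwhile improvement to one component of reach. It does not undermine the all-user description or the study as a whole.

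**What to change.** 1. Make the comparison with the OUD and fatal-overdose populations by user type, using self-reported age and gender of survey respondents who visit for themselves. Outcomes and Measures already has the survey collecting age, gender and the self/other item.
2. State beside that table that respondents are self-selected, as the article concedes, and that visiting for oneself is only a proxy for OUD, since the article also expects visits out of curiosity.
3. Keep the all-user Google Analytics demographics for description and for the general-population comparison. The split table supplements them and does not replace them.
4. Narrow the sentence in Recruitment, Sample, and Participants so that it does not claim that all-user data show representativeness of people with OUD.

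The cost is one additional table and a change of wording. The price in information is a smaller, self-selected denominator. Geography can be compared by user type only if the survey records location. Table 2 attributes location to Google Analytics and the survey jointly, while the text names only age and gender as examples of the survey's demographic items, so this needs to be settled.

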### Outcomes and Measures

To evaluate the safety and acceptability of the *MOUD Hub*, we will conduct pilot focus groups with 10 graduate students belonging to recovery groups or unions for people who use drugs. We will lead 2 focus groups to explore safety-related issues, along with gaining feedback on the acceptability, content, and any additional information that should be provided on the website. Safety concerns will focus on, but will not be limited to, information that may potentially be triggering or misleading and stigmatizing language.

A total of 4 additional focus groups will be conducted with other groups to gain more in-depth knowledge on the acceptability of the hub, user experience, and thoughts on its usefulness, following improvements from the pilot focus group. The topic guide in Multimedia Appendix 3 will be used.

To evaluate the reach and use patterns of the website, we will use Google Analytics to collect data on the number of users, their characteristics, and their interactions with the website [38,39]. The website will be launched in January 2025, and we will collect data for evaluation for a year and look at the data in 3-month increments. With this iterative approach, we can adjust the website in real time.

Our protocol’s outcomes and measures are shown in Table 2. We will first assess the dissemination reach of the website. The reach of an intervention is defined as “the absolute number, proportion, and representativeness of individuals who are willing to participate in a given initiative, intervention, or program, and reasons why or why not” [40].

**Table 2 table2:** Outline of the quantitative and qualitative measures that will inform the outcomes. Each measure is labeled with the information’s source.

Reach		Acceptability
